## Abstract

Background: Non-small-cell lung cancer (NSCLC) is a common, steady growing lung tumour that is often discovered when a surgical approach is forbidden. For locally advanced inoperable NSCLC, the clinical approach consists of a combination of chemotherapy and radiotherapy, eventually followed by adjuvant immunotherapy, a treatment that is useful but may cause several mild and severe adverse effect. Chest radiotherapy, specifically, may affect the heart and coronary artery, impairing heart function and causing pathologic changes in myocardial tissues. The aim of this study is to evaluate the damage coming from these therapies with the aid of cardiac imaging. Methods: This is a single-centre, prospective clinical trial. Patients with NSCLC who are enrolled will undergo computed tomography (CT) and magnetic resonance imaging (MRI) before chemotherapy 3 months, 6 months, and 9–12 months after the treatment. We expect to enrol 30 patients in 2 years. Conclusions: Our clinical trial will be an opportunity not only to highlight the timing and the radiation dose needed for pathological cardiac tissue changes to happen but will also provide useful data to set new follow-up schedules and strategies, keeping in mind that, more often than not, patients affected by NSCLC may present other heart- and lung-related pathological conditions.

## 1. Introduction

Non-small-cell lung cancer (NSCLC) is one of the most prevalent lung tumours and is responsible for a significant proportion of cancer-related deaths and illnesses worldwide [1]. Despite global efforts to increase awareness and early detection, a considerable number of NSCLC patients still receive a diagnosis only at advanced stages of the disease, which negatively affects their prognosis and treatment options. According to recent statistics, around 20% of NSCLC cases are diagnosed at advanced stages [2,3]. The late diagnosis of NSCLC results in a great deal of heterogeneity in terms of prognosis and treatment as patients may be eligible for surgery, chemotherapy, radiotherapy, or a combination of these treatments. Modern therapies have been able to achieve unprecedented survival rates, with increasing numbers of patients experiencing long-term remission [4,5,6,7]. However, this success comes at a cost, with numerous side effects associated with these therapies, including radiation-induced toxicity to the heart and coronary vessels [8,9,10,11]. Patients who undergo radiotherapy may experience a significant reduction in their perceived quality of life due to cardiac side effects. However, there is still a general lack of evidence and no universally approved threshold value for the relationship between radiation exposure and the manifestation of clinical side effects involving the cardiac muscle. This lack of evidence makes it challenging to prevent such side effects [12,13,14,15,16]. It is essential to adopt a clinical approach that focuses on maintaining acceptable quality of life for NSCLC patients undergoing treatment, with particular attention paid to managing the numerous side effects associated with modern therapies.

### Study Rationale

In light of the potential cardiac side effects associated with modern NSCLC therapies, cardiac imaging techniques such as cardiac computed tomography (cardiac-CT) and cardiac magnetic resonance (cardiac-MRI) may provide valuable information that could facilitate the tailored management of patients undergoing treatment. Cardiac MRI is considered the gold standard for evaluating ejection fractions and plays a pivotal role in the assessment of myocardial fibrosis [17,18,19,20,21,22,23,24]. Additionally, T2 sequences can easily detect oedema, which may reveal acute myocardial damage [25]. Cardiac-CT, on the other hand, offers greater spatial resolution, allowing for a better understanding of a patient’s anatomy. Furthermore, it can quantify the volume of non-calcified plaques and the extent of coronary stenosis in both symptomatic and asymptomatic patients [26,27]. The combined use of both these techniques may be useful for detecting early and late changes in cardiac vessels and the ventricular muscle. When a baseline examination acquired before treatment is available for comparison, these techniques become even more useful. Given the heterogeneity of cardiac side effects associated with NSCLC treatment and the lack of validated dose constraints in modern radiotherapy, studies using cardiac imaging techniques may be beneficial for understanding radio-induced cardiac toxicity. This information could lead to new opportunities for managing patients and improving their quality of life during treatment.

## 2. Materials and Methods

This prospective study will span fifteen months and will focus on evaluating the acute and chronic cardiac toxicity associated with thoracic radiotherapy by using advanced imaging techniques such as cardiac-MRI and cardiac-CT in patients with NSCLC. In addition to assessing cardiac toxicity, the study will also consider overall survival, disease-free survival, and locoregional control, as well as cardiac dosimetry parameters. The ultimate goal of this study is to use the data collected to predict the cardiological toxicity associated with adjuvant radiotherapy delivered with modern techniques. Furthermore, the study will seek to define the role of imaging methods in the prevention of cardiac risk in the neoadjuvant setting. It is expected that the results of this study will be beneficial for clinicians and researchers alike, providing valuable insights into the cardiac side effects of NSCLC treatment and potential strategies for mitigating those risks. Along with advanced imaging techniques, the study will also collect blood samples for the analysis of serum biomarkers. This approach will enable researchers to relate any pathological changes observed on the imaging studies with corresponding changes in serum biomarkers, providing a more comprehensive understanding of the mechanisms underlying cardiac toxicity in NSCLC patients undergoing radiotherapy [28,29,30,31].

### 2.1. Primary Endpoint

To evaluate early and late myocardial and coronary damage due to radiotherapy.

### 2.2. Secondary Endpoints

To evaluate progression-free survival (PFS).Local control evaluation.Overall survival evaluation.Cardiac, pulmonary, and oesophageal evaluation.

### 2.3. Inclusion Criteria (Table 1)

The histological diagnosis of non-small-cell lung neoplasm.Patients undergoing radiotherapy treatment with radical intent or with adjuvant intent. Intensity-modulated radiation therapy (IMRT) or the volumetric modulated arc therapy (VMAT) technique.

**Table 1 diagnostics-13-01717-t001:** Inclusion and exclusion criteria in CARE-RT trial.

Inclusion Criteria	Exclusion Criteria
• Histological diagnosis of non-small-cell lung cancer	• Metastasis in more than one pulmonary lobe
• Radiotherapy treatment: IMRT or VMAT	• Previous chest radiotherapy
	• Clinical progrssion during postoperative chemotherapy
	• Recent heart/lung disease

### 2.4. Exclusion Criteria (Table 1)

Documented metastases in a different lobe.Previous chest radiotherapy.Clinical progression during postoperative chemotherapy.Recent (inferior to 6 months) heart disease or severe lung disease.

### 2.5. Study Setting

The present prospective study has the potential to contribute valuable insights and data for various purposes related to NSCLC patients undergoing chemo-radiotherapy.

Firstly, it can shed light on the epidemiology of cardiac function in this specific population, revealing that NSCLC patients often fall under certain demographic categories such as being males, current smokers, and above 60 years old. The findings of this study can help with developing future prevention strategies for this vulnerable group.

Secondly, the study can provide a basis for the early post-treatment evaluation of the effect of chemo-radiotherapy on cardiac functionality. This can be crucial in developing future cardiac-sparing strategies, ensuring that the treatment does not cause adverse effects on the cardiac health of the patient.

Thirdly, the study can help in the late post-treatment evaluation of cardiac functionality after chemo-radiotherapy, which can be important in tailoring the follow-up of cancer survivors and preventing cardiac events in this population. Regular follow-up can help detect any adverse effects on cardiac function and implement appropriate measures to prevent further deterioration.

The delta analysis, which takes into consideration the differences between late and early post-treatment imaging and baseline imaging, will be pivotal in quantifying the effects of chemo-radiotherapy in patients with NSCLC. This analysis can help develop future strategies to prevent cardiovascular side effects and establish an effective follow-up plan for these patients.

A complete evaluation of the serum biomarkers’ ability to assess the development of cardiac functionality impairment is required. This task can be performed through the evaluation of changes in endothelial progenitor cells (EPCs) levels before and after treatment. In fact, EPCs represent an integral component of cardiovascular homeostasis, participating in the process of endothelial repair after vascular injury. Reduced levels of EPCs were associated with a significant increased risk of cardiovascular events, all-cause death, and onset/progression of microangiopathy [32]. The assessment of circulating levels of EPCs will be performed on fresh blood samples. Peripheral blood cells will be analyzed for the expression of surface antigens CD34+, KDR+, and CD133+ by direct flow cytometry. Quantitative analysis will be performed on a BD FACSCalibur cytometer (Becton-Dickinson), and 1,000,000 cells will be acquired in each sample. With this task, we will evaluate whether radiotherapy may impair endothelial function and reduce EPCs levels, increasing the risk of cardiovascular events.

A special database has been developed to list the data obtained through our study. The variables that will be collected are summarized below:Data scope;Personal data such as gender, age, and date of recruitment;Clinical history with special care for comorbidity and smoking habit;General status assessment Eastern cooperative oncology group (ECOG) performance status;TNM, histology, and molecular diagnostics;Radiotherapy treatment, possible concomitant or sequential chemotherapy;Response to therapy according to RECIST criteriaRadiotherapy parameters (technique, total dose, dose per fraction, volumes, start/end date, V5, V30, MeanDose, DMAX Cardiac Dosimetry, MeanDose Pulmonary Dosimetry, V20, V30, MeanDose Esophageal Dosimetry, V50, and V55);CT parameters (calcium score, thrombosis, and calcified plaques)Cardiac-MRI parameters (tissue evaluation, ventricular functional analysis, valve condition, and atrial dimension);Acute and late toxicity according to common terminology criteria for adverse events (CTCAE) 4.0 scales;Clinical outcomes overall survival (alive, deceased);Progression-free survival (progression yes/no, date of progression);Local control;Symptom control.

This research will measure two important outcomes: overall survival and progression-free survival. Overall survival refers to the amount of time from surgery to death, while progression-free survival refers to the amount of time from surgery to the point when the disease starts to progress. To analyze these outcomes, we will use the Kaplan–Meier method. This is a statistical method commonly used in medical research to estimate the probability of survival over time. By applying this method to the data collected from the study participants, the researchers will be able to determine the overall and progression-free survival rates for the group. In addition to analyzing survival rates, the study will also assess the acute and late toxicity of the radiotherapy treatment. Acute toxicity refers to any adverse effects that occur during or immediately after treatment, while late toxicity refers to adverse effects that occur at least 6 months after the end of treatment. The physicians involved will report the crude incidence rates of these toxicities, which will provide important information about the safety and tolerability of the treatment. To evaluate the impact of the treatment on cardiac function and coronary involvement, CT-scan and cardiac-MRI imaging will be performed. This will allow one to assess the function of the heart and its blood vessels before, during, and after treatment. The researchers will evaluate these factors at multiple time points: before treatment, 6 months from the beginning of treatment, 9 months from the beginning of treatment, and after 12–15 months from the end of treatment. Finally, quantitative methods to evaluate any early and late effects of the treatment on cardiac functionality will be used. This will provide additional insights into the potential long-term impact of the treatment on the heart and its function. Overall, this study aims to provide valuable information about the efficacy and safety of radiotherapy treatment for a specific tumour type, as well as its potential impact on cardiac function and coronary involvement. By analyzing multiple outcomes and using advanced imaging techniques, we believe we will gain a comprehensive understanding of the effects of targeted radiotherapy.

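### OS and PFS are timed from surgery although unoperated patients are eligible, and PFS as worded does not count death

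*Protocol article*

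**What the plan says.** Section 2.5 (Study Setting) of the protocol article defines both endpoints. For OS: "Overall survival refers to the amount of time from surgery to death". For PFS: "progression-free survival refers to the amount of time from surgery to the point when the disease starts to progress". The same paragraph names the Kaplan-Meier method and promises OS and PFS rates for the study participants as a whole, not for an operated subgroup. It mentions no delayed entry.

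The summary of collected variables, also in Section 2.5, describes the PFS data in the same terms: "Progression-free survival (progression yes/no, date of progression". It also lists the date of recruitment and the start and end dates of radiotherapy.

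Two statements on eligibility matter here. Section 2.3 admits "Patients undergoing radiotherapy treatment with radical intent or with adjuvant intent". Section 2.4 excludes "Clinical progression during postoperative chemotherapy".

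Section 2.2 lists PFS and OS as secondary endpoints. Section 2.1 makes myocardial and coronary damage the primary one.

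**The concern.** Three separate faults follow from the two definitions.

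1. **No time zero for some eligible patients.** Section 2.3 sets radical-intent radiotherapy against adjuvant radiotherapy. A patient irradiated with radical intent and never operated on has no surgery date, so neither endpoint has a starting point. The article offers no other origin.

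2. **Guaranteed time for the operated patients.** They join the study some time after surgery. Anyone who died in between could not be enrolled, and anyone who progressed on postoperative chemotherapy is excluded. A Kaplan-Meier curve that starts at surgery treats that interval as time at risk, although death (and, in part, progression) was ruled out by selection.

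3. **Death is not a PFS event.** As worded, the endpoint ends at progression alone, which makes it time to progression. A patient who dies without progression is either censored or left undefined.

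With about 30 patients expected, analysts applying the text would have to drop the unoperated patients or choose an origin ad hoc. The resulting curve would be hard to interpret.

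**Working it through.** The article states no survival rate, event count, surgery-to-entry gap or operated share, so there is no figure to reproduce. The first fault follows from setting the definitions beside the eligibility criteria. For the other two, the direction of bias can be checked under a constant hazard. **Every numerical input below is an assumption.**

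**Definitions against eligibility**

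| Patient | Surgery date | OS and PFS as defined |
|---|---|---|
| Radical intent, not operated | None | No time zero |
| Adjuvant | Yes, before entry | Defined, but the interval up to entry is guaranteed death-free |

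**Guaranteed time**

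Assume true survival of 70% at 12 months from surgery. The monthly hazard is h = −ln(0.70)/12 = 0.0297. If everyone enrolled has survived a gap of g months, and the curve still starts at surgery, the 12-month reading is exp(−h(12 − g)):

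- g = 2: exp(−0.0297 × 10) = 0.743
- g = 4: exp(−0.0297 × 8) = 0.788
- g = 6: exp(−0.0297 × 6) = 0.837

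So 70% reads 74%, 79% or 84%. The same formula with h = ln 2/median and the same 2 to 6 month gaps gives:

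| Assumed median | True 12-month rate | Reading |
|---|---|---|
| 12 months | 50.0% | 56.1% to 70.7% |
| 18 months | 63.0% | 68.0% to 79.4% |
| 24 months | 70.7% | 74.9% to 84.1% |

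The excess is about 4 to 21 points over this grid. It is upward for any g above zero and vanishes at g = 0 or with delayed entry.

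For OS the guarantee rests on being alive at entry. For PFS the exclusion in Section 2.4 adds freedom from progression, but only during postoperative chemotherapy. For an adjuvant patient who had no chemotherapy, the text does not guarantee a progression-free interval.

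**Death left out of PFS**

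Assume a 12-month progression risk of 35% and a 12-month risk of death without progression of 8% to 15%, acting independently. If deaths are censored, the curve reads 1 − 0.35 = 65%. With death counted it is:

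- 0.65 × 0.92 = 59.8%
- 0.65 × 0.85 = 55.3%

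The overstatement is about 5 to 10 points. If instead deaths make up 10% to 30% of PFS events, the three true rates in the table above give an overstatement of about 2.5 to 12 points.

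**The case against.** The strongest reply is that the sentence defining PFS is a lay explanation in a condensed article, and that event and censoring rules usually sit in the full protocol or analysis plan. This has some force on the third fault: the article never says that deaths will be censored. It does not remove the point. The definition is stated, not omitted; the variable summary repeats it; and nothing elsewhere adds death. Nor does it touch the origin, which is stated twice and conflicts with Section 2.3.

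Several stronger readings are tempting but are not supported:

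- *That the endpoints cannot be computed at all.* The recruitment date and the start of radiotherapy are among the listed variables, so a common origin is available. The fault lies in the definition, and no origin date is lost.
- *That dates of death or last contact are not recorded.* The list shows "Clinical outcomes overall survival (alive, deceased" without a date, but the article presents the list as a summary. Absence from it proves nothing.
- *That cardiac deaths are lost to the study.* They still count in OS, and toxicity is recorded separately. They drop out only of the endpoint called PFS.
- *That the whole cohort is inoperable.* The Abstract's "For locally advanced inoperable NSCLC" is background on usual care, not an eligibility criterion. Section 2.3 carries the argument.
- *That the percentages estimate this trial's bias.* They are hypothetical. With 30 patients and 70% survival the standard error is √(0.7 × 0.3/30) = 8.4 points, a 95% interval of about ±16 points, so many of the illustrated shifts lie within sampling error. The Abstract places baseline imaging before chemotherapy, so entry may come early and the gap may be short.

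It is also true that there is no comparator arm, so no treatment contrast is distorted. But sampling error is no defence of a systematic shift, and small gaps do not give an unoperated patient a surgery date.

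**Conclusion.** The point holds for the two secondary survival endpoints. The surgery origin contradicts the eligibility criteria and leaves unoperated patients without a time zero; this needs no assumption beyond radical-intent patients not all having had surgery. For operated patients the upward direction follows from selection at entry and from planning Kaplan-Meier without delayed entry. Its size cannot be derived from the article; 70% reading as 74% to 84% is an illustration that rests on a constant hazard and gaps of 2 to 6 months. PFS as worded is time to progression.

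This should be corrected before analysis, but it does not threaten the trial. No test or sample size in the article depends on OS or PFS, and the primary imaging endpoint is unaffected.

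**What to change.** Reword the two definitions in Section 2.5:

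- **Origin:** one date for all patients, either the start of radiotherapy or recruitment. Name one and use it for both endpoints.
- **OS:** time from that date to death from any cause.
- **PFS:** time from that date to the first of progression or death from any cause.
- **From-surgery analysis, if wanted:** adjuvant subgroup only, labelled as such, with delayed entry at enrolment so that patients count as at risk only from the day they join.

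The cost is a few sentences. Both candidate origins are already in the listed variables, so no new origin date has to be collected, and neither the imaging schedule nor the primary analysis changes.

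### The acute and late toxicity windows do not meet, so events between them enter neither reported rate; the crude rate has no stated denominator and may understate late toxicity if follow-up is incomplete

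*Protocol article*

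**What the plan says.** All of this is in the Protocol article; no analysis plan is shown. Section 2.5 Study Setting defines two windows.

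- Acute: "Acute toxicity refers to any adverse effects that occur during or immediately after treatment".
- Late: "late toxicity refers to adverse effects that occur at least 6 months after the end of treatment".

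The list of variables in the same section has one toxicity item, "Acute and late toxicity according to common terminology criteria for adverse events (CTCAE) 4.0 scales", with no intermediate class. The summary measure is stated as follows: "The physicians involved will report the crude incidence rates of these toxicities". No denominator is given, and nothing is said about patients who die or leave follow-up before month 6. Kaplan–Meier is named in that section, but only for overall and progression-free survival.

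Three other statements bear on the point.

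- The Abstract gives the imaging times as "before chemotherapy 3 months, 6 months, and 9–12 months after the treatment", whereas section 2.5 gives "before treatment, 6 months from the beginning of treatment, 9 months from the beginning of treatment, and after 12–15 months from the end of treatment".
- The Abstract says "We expect to enrol 30 patients in 2 years".
- Section 2 opens with "This prospective study will span fifteen months".

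**The concern.** There are two separate weaknesses.

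First, the definitions are not exhaustive. The acute window is closed by an adverb, not by a day or month, and the late window opens only at month 6. An event in between belongs to neither class, and rates are promised only for those two classes. The article supplies these definitions itself, so this is a rule that gives an incomplete result when followed as written; it is not a detail left to another document. Cardiac, pulmonary and oesophageal evaluation is a secondary endpoint (section 2.2), and these rates are its natural summary.

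Second, a crude proportion has no means of handling patients who have not been followed long enough to show late toxicity. If they stay in the denominator, they count as free of toxicity. The enrolment and duration figures make short follow-up plausible. What is at stake is a late-toxicity rate that looks better than it is, in a study meant to inform follow-up schedules.

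**Working it through.** The plan states no toxicity rate, death rate or dropout rate, so there is no figure to reproduce.

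**1. The windows.** Let t be months from the end of treatment, and let x be the unstated end of the acute window.

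- Acute covers t from treatment up to x. Late covers t ≥ 6. Unclassified: x < t < 6.
- The gap is at most just under 6 months, and shorter if x is read as some weeks.
- The Abstract's first post-treatment visit, at t = 3, lies before the late window.
- The section 2.5 visit at 6 months from the start of treatment must also precede t = 6. If radiotherapy lasts 6–7 weeks (assumption), it falls at 6 − 6/4.345 = 4.62 to 6 − 7/4.345 = 4.39 months after the end.
- So under either schedule there is a planned contact at which an adverse event could be found and have no clear class.
- Size: one event in 30 is 1/30 = 3.3 percentage points; two or three are 6.7 to 10 points.

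**2. The crude rate with complete follow-up.** Assumptions, none of them from the documents: constant death hazard h_d = ln 2/18 or ln 2/30 per month (median survival 18 or 30 months), and late-toxicity hazard h_t = −ln(0.80)/9 from month 6 (20% net risk over months 6–15).

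Cumulative incidence to month 15 over all enrolled, with death as a competing event, is

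F = exp(−6h_d) × h_t/(h_t + h_d) × [1 − exp(−9(h_t + h_d))].

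- Median 18: 0.794 × 0.392 × 0.434 = 0.135.
- Median 30: 0.871 × 0.518 × 0.350 = 0.158.

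When everyone is followed to death, toxicity or month 15, the crude proportion over all enrolled estimates this same F. A simulation of 200,000 patients agrees: crude 13.6% and 15.9%, Aalen–Johansen 13.5% and 15.7%. Deaths alone cause no bias in this quantity.

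**3. The crude rate with incomplete follow-up.** Let G(t) be the probability of still being under follow-up at t. The crude proportion over all enrolled then estimates

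∫ from 6 to 15 of h_t exp(−h_t(t − 6)) exp(−h_d t) G(t) dt.

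| Censoring (assumed) | Crude, median 18 | Crude, median 30 |
|---|---|---|
| None before month 15 | 13.5% | 15.8% |
| Uniform over months 12–15 | 11.7% | 13.6% |
| Uniform over months 9–15 | 9.7% | 11.1% |
| Uniform over months 3–15 | 5.5% | 6.3% |

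In the last row the simulation gave crude 5.7% and 6.4%, while Aalen–Johansen on the same censored data gave 13.7% and 15.9%. The estimator recovers the target; the crude proportion does not.

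**4. Does naming the denominator suffice?** Under censoring over months 3–15, the share alive and under follow-up at month 6 is 0.794 × 9/12 = 0.595, or 0.871 × 9/12 = 0.653. The crude rate among these patients is 0.0554/0.595 = 9.3% or 0.0634/0.653 = 9.7%. The risk among those alive at month 6 is 0.135/0.794 = 17.0% or 0.158/0.871 = 18.1%. Changing the denominator therefore does not repair censoring after month 6.

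**The case against.** **Deaths.** A reader might infer that crude incidence is biased because a patient who dies before month 6 cannot have late toxicity yet stays in the denominator. The documents do not support this. No denominator is stated, and step 2 shows that over all enrolled the crude proportion is a valid cumulative incidence when follow-up is complete. Moving to patients alive at month 6 raises the figure by the factor 1/S(6), where S(6) is survival to month 6. That answers a different question and corrects no bias.

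**Loss of events.** A reader might also infer that toxicity is unclassified for the whole of months 0–6, or that such events are lost. Both are too strong. The acute definition covers some unspecified first part of that time, and nothing says that the events go unrecorded; they have no reporting class.

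**Imaging.** A scan that falls between the windows does not leave its findings unanalysed. CT and MRI parameters are separate database items and are compared with baseline in the delta analysis of section 2.5. The gap concerns CTCAE adverse events.

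**Detail left elsewhere.** Denominators and the handling of short follow-up may be set out in a full protocol or analysis plan. That is fair for the denominator. It does not answer the windows, which the article defines, or the choice of a crude rate, which it states.

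**Follow-up.** Fifteen months may mean follow-up per patient, which would fit a last visit at 12–15 months. Follow-up could then be nearly complete and the crude rate close to correct. This stands as a reason to write that late toxicity may be understated, and not that it is.

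**Conclusion.** The gap between the windows is established from the text alone: an event after the undefined end of the acute window and before month 6 enters neither reported rate. How many events this affects cannot be estimated from the documents; at n = 30 each one is worth 3.3 points.

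The crude rate is a conditional weakness. It is sound over all enrolled if follow-up is complete. If follow-up is incomplete and those patients stay in the denominator, late toxicity is understated: from about 2 points under mild censoring (13.5% to 11.7%, or 15.8% to 13.6%) to less than half the true value under heavy censoring. These sizes rest wholly on assumed hazards and censoring patterns. That short follow-up will occur is plausible, given a fifteen-month span against 2 years of enrolment, but it is not stated. No claim is made that deaths alone bias the rate.

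**What to change.** 1. Make the windows contiguous at the protocol's own boundary. Acute/early runs from the start of radiotherapy to less than 6 months after its end; late is 6 months or more after its end.
2. Record the onset date with each CTCAE grade, and assign the class by onset date.
3. Report late toxicity as cumulative incidence (Aalen–Johansen) with death as a competing event and censoring at last follow-up.
4. Name the risk set: all enrolled, or those alive and under follow-up at month 6. Either is defensible, but they answer different questions, so the choice should be made before the data are seen. Give the number at risk beside each rate.

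The cost is the recording of onset dates, two reworded definitions and a slightly longer analysis. No visit, scan or treatment changes.
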